**Fig. 6 Fig6:**
[figure not shown]
Tests of Mediation. X = Treatment. M = Proposed Mediator. Y = 24-week outcomes. a = coefficient for correlation of X with M (M = aX). b = coefficient for correlation of M with Y (Y = bM). Y = c X = c’ + ab (the total effect of X on Y). M = a X (the effect of X on M). Y = c’ X + b M (direct effect of X on Y). a x b (mediation effect). Algebraic sign of a x b x c (type of mediation – complementary or suppressive)

We then will assess whether mediation is partial or complete, and whether it is complementary (i.e., the direct and mediated effects are in the same direction on the outcome Y and therefore have the same algebraic sign) or suppressive (the direct and mediated effects are in opposing directions on outcome Y and therefore have opposite signs). We will assess the significance of the direct effect (coefficient c_2_ in eq. 3): statistical significance of this term will signify that mediation by M is partial [206, 207]. We will also assess the algebraic sign of the product a*b*c to determine whether mediation is complementary or suppressive [206, 207].

Finally, a complex mediation model that jointly estimates multiple mediating outcomes and incorporates the correlations among mediators and joint effects of mediators on trial outcomes will ultimately be used to test and understand the mechanisms of the CBT and medication interventions on anxiety outcomes. Moderator effects of the Contextualizing Factors will be tested as described under “Heterogeneity of Treatment Effects”.

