(3) Group main effect ESs were then computed for a Stage 1 remission rate of 40%. Our estimated Stage 1 remission rate of 40% is a conservative estimate based on the CAMS remission rate of 35% achieved for ethnic minorities, when applying remission criteria less stringent than ours [30]. In CAMS, the 12-week remission rate was also approximately 10% higher in medication-only compared to CBT-only. We used this 10% difference in these calculations to compute ESs and resulting sample size estimates. For Main Effect 1 (start with medication vs start with CBT), ESs for all 3 medication or CBT groups (1: remitter; 2: non-remitter➔optimize monotherapy; 3: non-remitter➔medication+CBT) were computed as a weighted average of the group-specific ESs. Weights were the remission rate, with the non-remitter weight (1 minus remission-rate) split equally among the 2 randomized non-remitter groups (reflecting 1:1 Stage 2 randomization among non-remitters). For Main Effect 2 (among Stage 1 non-remitters, optimize Stage 1 treatment vs add the other treatment), ESs were computed as a weighted average of the ESs for monotherapy optimizers (medication+, CBT+) and a weighted average of the combined (medication+CBT, CBT + medication) groups. These weights were again 0.5*(1- remission-rate).

[4] We then computed the sample size required to detect Main Effect 2 (optimize monotherapy vs add the other therapy in non-remitters) at 80% power and tested at a 2-sided alpha = 0.05. From our computations above, the Main Effect 2 ES was approximately 0.40 SD, requiring a sample size of 194 participants among Stage 1 non-remitters. Increasing the sample size of 194 by the non-remission rate (N divided by non-remission rate) and by the estimated 20% dropout rate, yielded a sample size of 404 (202 per group) for Stage 1 remission rates of 40%. Randomizing 404 participants, with an estimated 324 finishing the trial and a remission rate of 40%, will provide the ability to detect an overall Main Effect 1 (medication first versus CBT first) ES of ≥0.31 SD with 80% power.

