### Mediation analyses

We will perform mediation analyses on the Stage 1 main intervention effects and will follow the literature for development of statistical approaches for mediation analysis of SMART design adaptive interventions. We will test whether the common and specific factors in our causal pathway model significantly mediate the associations of treatment with patient outcomes. Let X be the assigned treatment, Y be 24-week outcomes, and M be the proposed mediator **(**Fig. 6**)**. We will assess mediation using 3 regression equations: 1) *Y* = *c*_1_*X* + *e*_1_, assessing the association of treatment with 24-week outcomes; 2) *M* = *aX* + *e*_2_, assessing the association of treatment with the putative mediator; and 3) *Y* = *c*_2_*X* + *bM* + *e*_3_, associating the association of treatment with 24-week outcome when adjusting for the mediator (termed the “direct effect” of X with Y). Age and sex will be included as covariates in all three equations. We will test whether the estimator of the indirect effect (*a x b*) differs significantly from zero using bias-corrected bootstrapped confidence intervals on the estimator. A significant mediating effect suggests that the association of treatment effects (X) with trial outcomes (Y) in regression (1) is in part explained by treatment effects on mediating outcomes (M) in regression (3).

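### Complete mediation would be inferred from a non-significant direct effect, in a trial whose stated power does not cover that effect

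*Protocol article*

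**What the plan says.** The protocol article, Mediation analyses, begins "We will perform mediation analyses on the Stage 1 main intervention effects". It sets out three regressions: outcome on treatment (c_1), mediator on treatment (a), and outcome on treatment and mediator (c_2 and b). "Age and sex will be included as covariates in all three equations". The indirect effect a × b is tested "using bias-corrected bootstrapped confidence intervals on the estimator".

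After Fig. 6 the text continues: "We then will assess whether mediation is partial or complete". The only criterion it gives concerns c_2: "statistical significance of this term will signify that mediation by M is partial". No margin, interval rule or proportion mediated is attached to the word complete. A separate step uses the sign of the product of the coefficients to call mediation complementary or suppressive. A joint model with several mediators is to follow.

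The Sample size and power section sizes the trial for Main Effect 2. For the Stage 1 contrast, which the mediation analysis splits, it says that the planned numbers "will provide the ability to detect an overall Main Effect 1 (medication first versus CBT first) ES of ≥0.31 SD with 80% power". It gives no power for c_2.

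**The concern.** A significant c_2 does show that some of the effect bypasses the mediator, so that half of the rule is sound. The trouble lies in the other half. Once a × b is significant, a non-significant c_2 leaves only one of the two labels. Complete mediation asserts that no direct effect remains, and a p-value above 0.05 does not show that. The smaller or noisier the dataset, the more often the label would be reached.

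What is at stake is the mechanistic conclusion: whether alliance, exposure tolerance or coping efficacy explains all of a difference between starting with CBT and starting with fluoxetine. The section on factors specific to Coping Cat CBT itself expects alliance to mediate only part of the difference. Under this rule, that prediction can be confirmed only by a significant c_2.

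**Working it through.** **Inputs from the protocol (Sample size and power).** 404 randomised 1:1, 324 expected to finish (162 per arm), detectable total Stage 1 effect 0.31 SD at 80% power. A two-sided 5% level is stated for the sample size ("tested at a 2-sided alpha = 0.05") and is assumed here for c_2.

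**Assumptions.** Unit SD, equal arms, and chosen values for the total effect, the mediated share, a and b. The protocol states none of the mediation quantities.

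**Step 1: the plan's own figure.** Detectable effect = (1.960 + 0.842) × √(2/162) = 0.311 SD. The stated 0.31 reproduces; power at exactly 0.31 is 79.7%.

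**Step 2: precision of the direct effect.** If the mediator neither adds nor removes precision, SE(c_2) = 2/√324 = 0.111 SD. The miss rate is about Φ(1.96 − c_2/0.111). It passes 50% when c_2 falls below 1.96 × 0.111 = 0.218 SD (0.195 SD if all 404 are analysed).

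**Step 3: miss rates at 324 completers, same-direction mediation.**

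| Total effect (SD) | Share mediated | c_2 (SD) | c_2 non-significant |
|---|---|---|---|
| 0.31 | 10% | 0.279 | 29% |
| 0.31 | 20% | 0.248 | 39% |
| 0.31 | 30% | 0.217 | 50% |
| 0.31 | 50% | 0.155 | 71% |
| 0.31 | 70% | 0.093 | 87% |
| 0.40 | 50% | 0.200 | 56% |
| 0.50 | 50% | 0.250 | 39% |

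About 1,308 completers would give 80% power at c_2 = 0.155 SD.

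**Step 4: the rule as written.** In 1,000 simulated datasets per scenario, a × b was tested with a bias-corrected bootstrap (400 resamples) and c_2 with a t-test. Among datasets with a significant a × b, a non-significant c_2 (hence a wrong label of complete) occurred as follows.

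- Total 0.31 SD, half mediated: 70% (a = 0.40) or 66% (a = 0.31).
- Total 0.31 SD, other mediated shares: 82% at 70%, 49% at 30%, 42% at 20% and 34% at 10%.
- Half mediated, larger totals: 47% at 0.40 SD and 29% at 0.50 SD.

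**Step 5: does adding the mediator cost precision?** Not always. Collinearity multiplies the variance of c_2 by 1 + a²/4, while the mediator also removes residual variance. With a = 0.40, b = 0.50 and unit outcome SD within arms, the SE changes by √(1.04 × 0.75) = 0.883. The 50% threshold then moves from 0.218 to about 0.19 SD. That is why the simulated 47% lies below the tabulated 56%. With unit residual variance given M, a = 0.5 and b = 0.31 give √(1.0625/1.096) = 0.985, and a = 0.8 with b = 0.155/0.8 = 0.194 gives √(1.16/1.0375) = 1.057.

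**Step 6: suppression.** If the mediated path is −0.10 SD and the total 0.31 SD, then c_2 = 0.41 SD and the miss rate is about Φ(1.96 − 3.69) = 4%.

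**The case against.** The protocol never writes that a non-significant c_2 means complete mediation. It states only the valid direction, and the rest is inferred. That is true of the wording. But the section undertakes to choose between two labels and offers one test, so the inference is the only way to apply it. This is a stated rule, not detail left for an analysis plan.

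A reader might go further and infer that the trial would miss a real direct effect in most datasets, or that complete would be the usual answer whenever half or more of the effect bypasses the mediator. The documents do not support either. They give no direct effect, and the miss rate falls below one half once c_2 exceeds about 0.22 SD. The protocol's own hypotheses also allow suppression: fluoxetine is expected to do better overall, while alliance is expected to be greater with CBT and to go with better outcomes. The direct effect would then exceed the total and would rarely be missed. Nor does adding the mediator always reduce precision (Step 5).

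It is also fair that the single-mediator label is not the last word. A joint mediator model follows, and mediation is not among the specific aims and changes no primary or secondary comparison. This limits the importance of the point but does not make the rule sound.

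**Conclusion.** The point holds in limited form. The rule would declare complete mediation on a non-significant test of c_2, in a trial whose stated power covers a total Stage 1 effect of 0.31 SD and not the direct part. Non-significance is not evidence of no direct effect, whatever the true size.

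The practical size is conditional. Under same-direction mediation with 324 completers, direct effects below about 0.22 SD are missed more than half the time, which for a 0.31 SD total means about 30% or more mediated. For larger direct effects the rate is lower, and under suppression it can be small. These figures rest on assumed values of the total effect, mediated share, a and b, on unit SDs, and on a two-sided 5% test. Any false-discovery-rate control applied to c_2 under the Multiplicity section would raise the miss rates. Only a secondary mechanistic conclusion is affected.

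**What to change.** Delete the partial/complete label based on the p-value of c_2. Report a × b and c_2, each with a bootstrap 95% confidence interval, as the main mediation results. Give the proportion mediated only when the total effect is clearly non-zero and the direct and indirect effects have the same sign; otherwise it is unstable or has no meaning. State that a non-significant c_2 leaves the remaining direct effect undetermined and is not evidence of complete mediation.

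An equivalence margin of ±0.1 SD should not be put in its place. The 95% half-width is about 1.96 × 0.111 = 0.218 SD, and still about 0.19 SD with a = 0.40 and b = 0.50, so the interval would not fit even around an estimate of zero. With the 0.111 SD basis, a half-width of 0.1 SD needs (2 × 1.96/0.1)² ≈ 1,540 completers.

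The cost is a change of wording; the planned bootstrap can supply the intervals. The downside is that complete mediation will in practice not be claimable.

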Exposure also promotes the development of cognitive, emotion regulation, and behavioral skills for coping more effectively with fear, termed *coping efficacy.* Coping efficacy diminishes the conditioned fear response and provides the opportunity for new extinction learning, with an attendant inhibition of maladaptive avoidance. Practicing these skills in different fear-inducing contexts supports generalization of inhibitory learning and stronger extinction of fear responses [78]. Of note, both time spent in exposure tasks, and level of difficulty of the exposures tolerated, predicted better outcomes to *Coping Cat* within the CAMS sample [119]. These findings directly informed our decision to have additional exposure practice and mastery be the focus of our Phase 2 CBT optimization protocol. In addition, efficacy measures in the CAMS trial outperformed specific measures of cognitive change in mediational models on Coping Cat effects, suggesting that development of coping efficacy may mediate CBT outcomes [120].

We will obtain after each CBT session a therapist-rated measure of 3 key facets of exposure practice (quantity, difficulty level, and mastery of exposure tasks) [119], which we will use to craft an index of tolerance to exposure – a CBT-specific factor in effecting patient outcomes. As a complement to this in-session measure of tolerance of exposure, we will also obtain at baseline and then every fourth session the parent version of the 8-item *Child Anxiety Avoidance Scales* [110], a measure of the evolving real-world CBT skill set outside of session that assesses the reduction of anxious avoidance when presented with threatening stimuli. Finally, we will use our measure of Self-efficacy from the NIH toolbox measure of Life-Satistfaction as a proxy for coping efficacy to test this CBT-specfic pathway. We expect that measures of each of the common factors will independently and positively associate with outcomes in our study for both *Coping Cat* and medication therapies [72, 82, 121], and we expect that the greater therapeutic alliance anticipated with CBT compared with medication therapy will partially mediate differences in clinical outcomes across the two treatment modalities. We also expect that measures of the CBT *specific factors* -- exposure tolerance and coping efficacy -- will positively associate with clinical outcomes in response to *Coping Cat* CBT.

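### The rule for mediation type takes the sign of a×b×c with c the total effect, so it can label as complementary what the protocol's own definition calls suppressive

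*Protocol article*

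**What the plan says.** All references are to the Protocol article, section Mediation analyses and the Fig. 6 legend.

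- **Equations in the text.** Equation 1 regresses the 24-week outcome on treatment and gives the total effect, c_1 ("assessing the association of treatment with 24-week outcomes; 2"). Equation 2 gives a, the effect of treatment on the mediator. Equation 3 adds the mediator and gives b and the direct effect, c_2.
- **Definition of type.** Mediation is complementary when "the direct and mediated effects are in the same direction on the outcome Y and therefore have the same algebraic sign". It is suppressive when the two effects point in opposite directions.
- **Partial or complete.** This is judged from the direct effect: "We will assess the significance of the direct effect (coefficient c_2_ in eq. 3").
- **Rule for type.** "We will also assess the algebraic sign of the product a*b*c to determine whether mediation is complementary or suppressive". The c here has no subscript.
- **Legend.** Plain c is the total effect: "Y = c X = c’ + ab (the total effect of X on Y"). The direct effect has a prime: "Y = c’ X + b M (direct effect of X on Y"). The indirect effect is "a x b (mediation effect"). The legend then repeats the rule for type as the sign of a×b×c, without the prime.

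In the section Factors specific to Coping Cat CBT, the protocol adds that "we expect that the greater therapeutic alliance anticipated with CBT compared with medication therapy will partially mediate differences in clinical outcomes".

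**The concern.** The definition compares the direct effect with the mediated effect. The rule compares the total effect with the mediated effect. The total already contains ab, so it is pulled towards the sign of ab. When the mediated effect opposes the direct effect and is the larger of the two, the total takes the mediated effect's sign. The rule then reports agreement where the definition sees opposition.

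What is at stake is the description of mechanism. Suppose alliance helps CBT while some other route helps fluoxetine by a similar or smaller amount. The trial could then report that the two routes work in the same direction. The protocol allows for this setting: the section on the non-randomized TAU group says that the two treatments may produce similar responses, and Hypotheses for Aim 1 describes the earlier multimodal trial's advantage for medication as small and non-significant.

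**Working it through.** **1. Which c does the rule use?** The text defines only c_1 (total) and c_2 (direct). The only place that defines plain c is the legend, where it is the total effect and stands beside a separate c'. An analyst who follows the document as written would use the total.

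**2. Algebra.** With c = c' + ab,

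ab·c = ab·(c' + ab) = ab·c' + (ab)².

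- If ab and c' share a sign, both terms are positive and the rule agrees with the definition.
- If they oppose, ab·c' is negative, and the sum is positive exactly when |ab| > |c'|. The rule is then wrong.

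The legend's identity holds for least squares with age and sex in all three equations. In one simulated dataset of n = 324, a = 0.224077, b = 0.598727 and c_2 = −0.177065. So ab = 0.134161 and c_2 + ab = −0.042904, which equals the fitted c_1.

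**3. Worked values** (a = 0.5, b = 0.6, so ab = 0.30):

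| c' | c = c' + ab | ab·c | Rule | Definition |
|---|---|---|---|---|
| +0.20 | +0.50 | +0.15 | complementary | complementary |
| −0.10 | +0.20 | +0.06 | complementary | suppressive |
| −0.20 | +0.10 | +0.03 | complementary | suppressive |
| −0.30 | 0 | 0 | none | suppressive |
| −0.50 | −0.20 | −0.06 | suppressive | suppressive |

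With c' in the product, the second row gives 0.30 × (−0.10) = −0.03, suppressive, as the definition requires.

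**4. Behaviour at the trial's size.** The protocol gives no effect sizes for mediators, so those below are assumptions. Set-up: n = 324 completers (Sample size and power), 1:1, X = 1 for CBT first, and a higher Y is worse. Treatment shifts the mediator by a = 0.8 SD, and b = −0.3 (−0.4 in the second row), so ab favours CBT. Each scenario has 10,000 datasets. Ranges cover two scalings of the outcome: residual SD 1, or SD 1 given treatment. In every row the true type is suppressive. The last column counts trials in which a, b and c_2 are all significant at 5% (a stand-in for the planned bootstrap test of ab and the test of c_2) and the label is still wrong.

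| ab | c' | Total | Labelled suppressive using c | Using c_2 | Both effects significant, label wrong |
|---|---|---|---|---|---|
| −0.24 | +0.15 | −0.09 | 21–22% | 90–91% | 6–8% |
| −0.32 | +0.20 | −0.12 | 14–15% | 95–97% | 23–31% |
| −0.24 | +0.24 | 0 | 50% | 98% | 9–11% |
| −0.24 | +0.34 | +0.10 | 81–82% | >99% | 5–6% |
| −0.24 | +0.44 | +0.20 | 96% | >99% | 1.5% |
| −0.24 | +0.55 | +0.31 | >99% | >99% | 0.2% |

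The last total, +0.31, is the Main Effect 1 difference that the protocol says it can detect with 80% power.

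**The case against.** **The authors probably meant the direct effect.** The sentence just before the rule names c_2, and the definition is written in terms of the direct effect. This is plausible, and it makes the error look like one of notation. It does not remove it: the legend separates c from c' and then writes the rule with c. The methodological sources cited for the rule are not available here, so the meaning of c in them cannot be checked.

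**A reader might infer that the rule fails in the very case the protocol expects**, since hypothesis 1a favours fluoxetine overall and alliance is expected to favour CBT. The documents do not support that. If the total favours fluoxetine and ab favours CBT, then c and ab have opposite signs, a×b×c is negative, and the label is correctly suppressive. The last three table rows show this. The rule goes wrong when the total is null or favours CBT.

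**A reader might also take a mislabelling rate near 80% as what to expect.** That figure (100% minus 21–22% in the first row) belongs to one assumed scenario with a total favouring CBT, and it ignores the planned tests of ab and c_2. Counting only trials in which both effects are significant, it falls to 6–8%. The text does not make the label conditional on those tests, and in the second row the gated figure is still 23–31%. The defect shrinks but does not vanish.

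**The label is only descriptive.** This stands. Both ab and c_2 are estimated, so their signs can be read directly.

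**Conclusion.** The point holds as an inconsistency between a stated rule and a stated definition. It is not an omission that a statistical analysis plan would fill. The algebra is exact and needs no assumption beyond the legend's own meaning of c: the rule is wrong when the mediated and direct effects oppose and |ab| > |c'|, and it never errs when they agree. When they oppose and the total is near zero, the bare sign is close to a coin flip.

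How often this would happen in the trial cannot be stated, because it depends on mediator effects that the protocol does not give. The consequence is limited to the type label. Hypothesis tests, estimates, intervals, sample size, the bootstrap test of ab, and the primary and secondary analyses are untouched. Severity: minor.

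**What to change.** Replace a×b×c with a×b×c_2 in the text and with a×b×c' in the Fig. 6 legend. The rule then matches the definition by construction. The cost is one symbol in two places, with no new data or analysis.

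Optionally, add a sentence that the label is assigned only when the intervals for both ab and c_2 exclude zero, and that otherwise the two estimates are reported without a label. The reason is that a bare sign must give a label even when there is no direct effect. In the same simulation with c' = 0 (ab = −0.24 or −0.18), the rule with c says complementary in 94–98% of trials, and the sign of a×b×c_2 is itself about 50:50. The downside is that some mediators will carry no label.
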